## Statistical power and sample size calculations

The sample size calculation is performed using www.powerandsamplesize.com and is based on the primary outcome, length of hospital stay. The expected reduction in length of hospital stay is based on data from a previous study showing a reduction (3.9 days vs. 6.0 days) for patients hospitalized with CAP randomized to either early mobilization or standard usual care [18]. The number of patients with CAP is based on a 2-day difference in length of hospital stay between CAP patients receiving standard usual care compared to standard usual care combined with daily physical training. The standard deviation for this calculation is 3.5 days, as previous observed [18]. Assuming an estimated drop-out rate of 15%, inclusion of 210 patients (70 patients in each group) will provide a power of > 0.8 at a two-sided significance level of 0.025, adjusted for multiple comparisons (0.05/2).

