## Challenges and protocol changes due to the coronavirus disease (COVID)-19

Due to the COVID-19 pandemic and a national wide lockdown starting in March 2020, the study was suspended from March 13, 2020, to April 21, 2020. The recruitment process was again suspended from December 7, 2020, to January 4, 2021, due to the second national wide lockdown. After the second lockdown, the steering committee decided to expand the study inclusion to patients with COVID-19 CAP. As COVID-19 patients is isolated during hospitalization, the exercise sessions are limited to the patient rooms, meaning that especially the exercise booklet group is restricted to primarily strengthening exercises. The COVID-19 pandemic has resulted in missed follow-up visits both hospital and home visits as patients have been unwilling to engagement in research-related activities due to the risk of being exposed to COVID-19. Moreover, follow-up visits are performed more often as home visits.

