### Pre-planned analysis

Available-case analyses will be carried as the main aim is to evaluate the efficacy of the interventions. This means that patients will contribute to the statistical analyses until they drop-out or the study is terminated. Also, as patient drop-out in most cases will be caused by factors, which will happen independently of this study, missing at random will most likely be an acceptable assumption. Additionally, subgroup analyses for patients without COVID-19 CAP will be carried out as patients with COVID-19 CAP may stay longer at the hospital.

For the primary outcome (length of hospital stay), analysis of covariance will be performed to quantify differences between groups. The following covariates will be included in the model: age, gender, CURB-65 score, BMI, and total number of comorbidities (categories 0, 1, 2, > 2). The estimated mean difference (in changes) between the standard usual care group and the two exercise groups (standard usual care vs. exercise booklet and standard usual care vs. in-bed cycling) with the corresponding adjusted confidence interval (CI) and *p* values will be reported. Both CIs and *p* values will be adjusted utilizing correlations between estimates and tests in a less conservative way compared to Bonferroni adjustment [36].

Survival analysis with Kaplan-Meier estimation and Cox proportional hazards regression will be performed to explore differences between groups in time to readmission. Hazard ratios comparing the standard usual care group with the two exercise groups (standard usual care vs. exercise booklet and standard usual care vs. in-bed cycling) will be estimated and reported together with corresponding CIs and *p* values. Kaplan-Meier estimation and Cox proportional hazards regression will be performed to explore differences between groups in time to mortality. Hazard ratios comparing the standard usual care group with the two exercise groups (standard usual care vs. exercise booklet and standard usual care vs. in-bed cycling) will be estimated and reported together with corresponding CIs and *p* values. For readmission, data will be censored 3 months after discharge, while for mortality, censoring will occur 6 months after discharge.

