For secondary outcomes (total lean mass, total fat mass, total fat-free mass, leg lean mass, trunk fat mass, EQ-5D-5L score, Barthel Index-100 score, grip strength, 30-s CST, systemic inflammation, and physical activity [AX3]), linear mixed models with treatment by time interaction as a fixed-effects term and patient-specific random intercepts will be fitted to explore differences in changes from baseline between groups. Specifically, the estimated mean difference (in changes) between the standard usual care group and the two exercise groups (standard usual care vs. exercise booklet and standard usual care vs. in-bed cycling) with corresponding CIs and *p* values will be reported. Logarithm transformations will be applied where appropriate (to handle right-skewed distributions), and resulting estimates and CIs will be back-transformed accordingly.

Likewise, for exploratory outcomes (glucose metabolism), linear mixed models with treatment by time interaction as a fixed-effects term and patient-specific random intercepts will be fitted to explore differences in changes from baseline between groups. Specifically, the estimated mean difference (in changes) between the standard usual care group and the two exercise groups (standard usual care vs. exercise booklet and standard usual care vs. in-bed cycling) with corresponding CIs and *p* values will be reported.

For other categorical outcomes (IPAQ score, diabetes status, and frailty score), differences between groups at 3 months will be explored by the chi-squared test (r × c tables) and expressed as counts and percentages, and *p* values will be reported. In all statistical analyses, *p* values < 0.05 will be considered significant.

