### Randomization: sequence generation and allocation concealment

Patients are randomly assigned (1:1:1) in permuted blocks according to computer-generated random numbers (R version 3.4.1), to undergo either standard usual care or booklet exercise or in-bed cycling. The randomization is performed at the day of inclusion (within 24 h of admission) after patients have provided informed consent to participate (additional file 2). No stratification factors are used in the randomization algorithm. The randomized sequence is generated centrally by a researcher not involved in the testing. The allocation is delivered to the researcher responsible for the exercise interventions in sealed envelopes at the time of inclusion. Patients are informed about their allocation after baseline assessment (at days 0 or 1) has been completed. The researcher performing the baseline assessment is responsible for informing the patients about their allocation. The study allocation is blinded for the nurses, physiotherapists, and clinicians treating the patients; however, the researcher responsible for the exercise intervention and outcome assessor is unblinded. Even though blinding could limit the occurrence of bias when collecting and assessing data, the researchers involved in this study has no influence on treatment plans or evaluation of readiness for discharge. The risk of bias due to lack of blinding is therefore evaluated to be relatively low.

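### The primary ANCOVA of length of stay leaves out COVID-19 status, giving up precision in a design whose stated power has almost no margin

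*Protocol article*

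**What the plan says.** - **Primary model** (Pre-planned analysis). Length of stay is analysed by ANCOVA, and adjusted mean differences are reported for each exercise arm against usual care. "The following covariates will be included in the model: age, gender, CURB-65 score, BMI, and total number of comorbidities". COVID-19 status is absent.
- **COVID-19** (Pre-planned analysis). The only provision is a subgroup analysis of patients without COVID-19 CAP, on the ground that "patients with COVID-19 CAP may stay longer at the hospital".
- **Admission of these patients** (Challenges and protocol changes due to COVID-19). After the second lockdown, "the steering committee decided to expand the study inclusion to patients with COVID-19 CAP". The expected share is not given.
- **Allocation** (Randomization). "No stratification factors are used in the randomization algorithm".
- **Sizing** (Statistical power and sample size calculations). The number of patients is "based on a 2-day difference in length of hospital stay between CAP patients receiving standard usual care" and the same care plus daily training. "The standard deviation for this calculation is 3.5 days, as previous observed", the source being an earlier trial of early mobilisation in CAP. With 15% drop-out, 70 per arm is said to give power above 0.8 at two-sided 0.025. This section does not mention COVID-19.

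**The concern.** The plan names a factor that may predict the primary outcome, admits patients with that factor mid-trial, does not stratify on it, and then leaves it out of an explicit covariate list. Because the list is spelled out, this is a choice the article has made and not a detail left for later.

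If COVID-19 patients do stay longer, the difference between the two kinds of patient stays in the residual variance of the primary model. Confidence intervals widen and power drops. The subgroup analysis does not recover this: it leaves the primary estimate as it is and uses fewer patients. What is at stake is precision on the primary outcome in a design with very little to spare.

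**Working it through.** **Inputs from the article:** difference 2 days, SD 3.5, two-sided alpha 0.025, power 0.80, drop-out 15%.

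**1. The plan's own figure.** With z(0.9875) = 2.241 and z(0.80) = 0.842:

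n per arm = 2 × (2.241 + 0.842)² × 3.5² / 2² = 58.2, so 59. Then 59 / 0.85 = 69.4, so 70 per arm and 210 in total. This matches.

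Power at 59 per arm = Φ(2 / (3.5 × √(2/59)) − 2.241) = Φ(0.862) = 0.806. A noncentral t calculation gives 0.796. With all 70 analysed, the normal formula gives 0.873.

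**2. The margin.** The largest residual SD that keeps power at 0.80 is 2 × √(n/2) / 3.083:

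- 59 per arm: 3.52 days, so the variance can rise by 3.523² − 3.5² = 0.16.
- 70 per arm: 3.84 days, so it can rise by 3.838² − 3.5² = 2.48.

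**3. Effect of leaving COVID-19 status out.** Take 3.5 as the SD within each kind of patient, p as the COVID-19 share and d as the extra mean days. Both p and d are assumptions. Then SD = √(3.5² + p(1 − p)d²). No credit is given for the five listed covariates.

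| p | d | p(1 − p)d² | SD | Power, 59/arm | Power, 70/arm |
|---|---|---|---|---|---|
| 10% | 2 | 0.36 | 3.55 | 0.793 | 0.862 |
| 10% | 5 | 2.25 | 3.81 | 0.730 | 0.807 |
| 20% | 2 | 0.64 | 3.59 | 0.784 | 0.854 |
| 20% | 3 | 1.44 | 3.70 | 0.756 | 0.831 |
| 20% | 4 | 2.56 | 3.85 | 0.719 | 0.798 |
| 30% | 4 | 3.36 | 3.95 | 0.694 | 0.774 |
| 30% | 5 | 5.25 | 4.18 | 0.639 | 0.721 |

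**4. Effect of putting it in.** The term p(1 − p)d² leaves the residual variance, so the formula returns 0.806 at 59 per arm. A simulation with lognormal stays (means 6 and 4 days, 59 per arm, p of 10–30%, d of 2 or 4) gave power of 0.70 to 0.79 without the covariate and 0.79 to 0.80 with it.

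**5. The subgroup alone.** If 20% or 30% of the 59 per arm are set aside, about 47 or 41 remain. Power within the subgroup at SD 3.5 is then about 0.70 or 0.64.

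**The case against.** A reader might infer that the stated power is unlikely to hold. The documents do not show that, for these reasons:

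- The figure reproduces, and any shortfall depends on a share and an excess stay that the article does not give.
- High shares need many COVID-19 patients late in the trial. From 1 April 2019 to 1 March 2022, less the two suspensions, there are about 998 recruiting days, of which about 421 (42%) fall after 4 January 2021. With even recruitment, an overall share of 20–30% needs 47–71% of the later patients to have COVID-19.
- Length of stay comes from patient files, so loss may be below 15%. At 70 per arm, several of the scenarios stay above 0.80.
- The listed covariates earn no credit above. If they explain 5% or 10% of the variance, power at SD 3.5 and 59 per arm is 0.827 or 0.849, which absorbs p(1 − p)d² up to about 0.78 or 1.39. That covers 20% with 2 extra days (0.64). It does not cover 30% with 4 extra days, where power is 0.733 even at 10%.
- The planned multiplicity adjustment is less conservative than the 0.025 used for sizing.

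All of this stands, and it limits the point to lost precision and thin margin.

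Three other strong readings also fail. The article says that COVID-19 patients *may* stay longer, not that they do. Chance imbalance in COVID-19 share is not bias: it is random variation that the standard error already carries, and it should not be counted again on top of the power loss.

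Nor does right skew make the analysis in days unsound. The planning means of 3.9 and 6.0 days with SD 3.5 do suggest skew, and log transformation is mentioned only for the secondary mixed models, where appropriate. But with simulated lognormal stays and SD 3.5 (common or pooled), raw-scale power is 0.79 to 0.83 and type I error 0.0235 against 0.025. Log analysis gives 0.90 to 0.99 in the same simulations, but it answers a different question. With means 4 and 6 and SD 3.5 in both arms, the ratio of geometric means is 0.58 while the ratio of means is 0.67. The sizing, Table 2 and the reported effect are all in mean days.

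**Conclusion.** The point holds as a precision point. A factor that the plan itself connects with length of stay is missing from a fixed covariate list, and adding it is close to free. The randomised comparison remains unbiased without it.

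The stated power is correct on its own inputs but tolerates a residual SD of only about 3.52 days at 59 per arm (3.84 at 70), and the sizing section gives no sign of having been revisited when the population was widened. Under the assumed range of 10–30% COVID-19 patients and 2–5 extra days, with no credit for other covariates, power without the covariate is 0.79 to 0.64 at 59 per arm and 0.86 to 0.72 at 70. With it, power is about 0.80 at 59. These figures show sensitivity and do not forecast a shortfall.

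**What to change.** 1. Add COVID-19 status (yes/no) to the five covariates of the primary ANCOVA, prespecified before analysis.
2. Keep the subgroup analysis of patients without COVID-19 CAP as an addition.
3. State beside the sample size that power above 0.8 rests on SD 3.5 from a previous CAP trial and was not revisited after COVID-19 patients were included.
4. Keep the difference in mean days as the primary estimate. A log-scale analysis of length of stay is at most an optional supporting analysis.

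The cost is one degree of freedom and a less comfortable power statement. No new data are needed, because the planned subgroup analysis already requires each patient's COVID-19 status. Recruitment was still open when the article appeared, so the change could be prespecified.

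### The readmission and mortality Cox models leave out the baseline covariates already used in the primary model, which gives up some power, mainly for readmission

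*Protocol article*

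**What the plan says.** All of this is in the protocol article. Under Pre-planned analysis, the primary length-of-stay outcome has an analysis of covariance: "The following covariates will be included in the model: age, gender, CURB-65 score, BMI, and total number of comorbidities", the last in four categories. The same section then turns to readmission: "Survival analysis with Kaplan-Meier estimation and Cox proportional hazards regression will be performed". It asks for hazard ratios of usual care against each exercise group with confidence intervals and p values, and repeats this for mortality. Neither Cox model is given covariates, and nothing says that the primary set carries over. Readmission is censored at 3 months and mortality at 6 months after discharge.

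On randomisation: "No stratification factors are used in the randomization algorithm". On the threshold for these analyses: "In all statistical analyses, *p* values < 0.05 will be considered significant".

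**The concern.** The two time-to-event outcomes head the list of secondary outcomes, and age, severity and comorbidity are natural candidates to predict both. The trial already needs these baseline values for the primary model. The sample size was set on length of stay alone, so the hazard-ratio comparisons start with limited power.

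In a Cox model, omitting a strong prognostic factor moves the estimated hazard ratio toward 1. Without stratification, a chance difference between arms in age or severity also feeds straight into the unadjusted estimate. If the text is followed as written, the main hazard ratios are unadjusted, and an adjusted one added later would look post hoc.

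**Working it through.** **The plan's own figure.** Inputs from Statistical power and sample size calculations: difference 2 days, SD 3.5 days, two-sided alpha 0.025, drop-out 15%.

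- n per arm = 2 × (2.241 + 0.842)² × 3.5² / 2² = 58.2, so 59. Power at 59 per arm is 0.806.
- 59 / 0.85 = 69.4, so 70 per arm and 210 in total.

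The plan's claim that 210 patients "will provide a power of > 0.8" reproduces. No event count or power is stated for the Cox models. I therefore use 59 per arm (15% loss applies) to 70 per arm (patient files give complete follow-up).

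**Events available against events needed** (two-sided alpha 0.05). For a hazard ratio of 0.5 and 80% power, Schoenfeld's formula gives 4 × (1.960 + 0.842)² / (ln 0.5)² = 65.3, so 66 events per pairwise comparison. With 140 × 0.85 = 119 evaluable patients per comparison:

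- Mortality, if the 14% in Background applies: 0.14 × 119 = 16.7 deaths, power about 0.29. Over three arms, 0.14 × 178.5 = 25 deaths, or 0.14 × 210 = 29 without loss. Background gives no time frame for the 14%.
- Readmission: Background gives one in five at 30 days and no 90-day rate. Assuming 20-40%: 24 to 48 events, power 0.39 to 0.67.

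**Effect of adjustment on readmission power.** Simulated three-arm trials, 1500 replicates, Monte Carlo standard error about 0.013. The control rate, hazard ratio and SD of the prognostic log-hazard score are all assumptions.

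| Per arm | Control rate | True HR | Score SD | Covariates | Unadjusted | Adjusted |
|---|---|---|---|---|---|---|
| 59 | 30% | 0.5 | 0.5 | 7 df | 0.385 | 0.405 |
| 59 | 30% | 0.5 | 1.0 | 7 df | 0.334 | 0.438 |
| 59 | 35% | 0.45 | 0.7 | 3 | 0.53 | 0.60 |
| 59 | 35% | 0.45 | 1.0 | 3 | 0.46 | 0.60 |
| 70 | 30% | 0.5 | 0.7 | 3 | 0.43 | 0.47 |
| 70 | 30% | 0.5 | 1.0 | 3 | 0.37 | 0.50 |
| 70 | 35% | 0.45 | 0.5 | 3 | 0.60 | 0.63 |
| 70 | 35% | 0.45 | 0.7 | 3 | 0.61 | 0.67 |
| 70 | 35% | 0.45 | 1.0 | 3 | 0.53 | 0.68 |

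A separate run of the strongest case gave 0.54 to 0.68, and one with a weak score gave 0.36 to 0.37. An 800-replicate repeat of the first row gave 0.414 to 0.422, so with a weak score the gain is close to nothing.

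**Attenuation and standard error** (59 per arm, 30%, HR 0.5). With score SD 1.0 the median log hazard ratio is -0.610 unadjusted (HR 0.54) and -0.747 adjusted (HR 0.47), while its standard error goes from 0.393 to 0.414. With SD 0.5: -0.666 to -0.719, standard error 0.403 to 0.418. The adjusted medians overshoot ln 0.5 = -0.693 a little, which is a reason for a short covariate list.

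**Mortality.** At 59 per arm, control 14%, HR 0.5 and 7 covariate df, power goes from 0.141 to 0.161 (SD 0.5) and from 0.145 to 0.183 (SD 1.0). The standard error goes from 0.627 to 0.644 and from 0.606 to 0.648. At 70 per arm the gain is 0-3 points for 14% and HR 0.5, and 2-8 points for 20% and HR 0.35.

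**False-positive rate.** With a true hazard ratio of 1, rejection was 0.032-0.053 unadjusted and 0.037-0.058 adjusted. The gain is not bought with a clearly inflated error rate.

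**Chance imbalance.** At 70 per arm a standardised covariate difference has SD √(2/70) = 0.17, so 1.96 × 0.17 = 0.33 is within the ordinary range. With score SD 0.7 this shifts the log hazard ratio by 0.7 × 0.33 = 0.23, a factor of 1.26.

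**How many covariates the data carry.** The full primary set takes 7 df with CURB-65 linear, plus 2 treatment terms, so 9 parameters: 25 / 9 = 2.8 deaths per parameter. Age and CURB-65 plus treatment is 4 parameters: 25 / 4 = 6.3.

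**The case against.** **Scope.** A journal article often leaves covariate lists for secondary models to a fuller plan, the text never calls the Cox models unadjusted, and it presents them as exploratory. This lowers the weight of the point. It does not remove it: the section goes outcome by outcome, names covariates for one model and gives none for the next two.

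**Validity.** A reader might infer that unstratified randomisation makes the unadjusted hazard ratios biased. It does not. Randomisation protects them, the unadjusted false-positive rate above is not inflated, and the unadjusted hazard ratio estimates a legitimate marginal quantity. Chance imbalance is already part of its sampling error.

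**Precision.** A reader might expect narrower intervals. In the Cox model the standard error of the log hazard ratio rises slightly; power improves because the estimate moves away from 1.

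**Mixed models.** A reader might extend the point to the continuous outcomes, where "linear mixed models with treatment by time interaction as a fixed-effects term and patient-specific random intercepts will be fitted", and apply 1/(1 - R²) - 1 to claim that covariates with R² of 10-20% are worth 11-25% more patients. That formula belongs to a single-outcome analysis of covariance. Here the target is change from baseline, and the baseline measurement and random intercept already absorb stable differences between patients. In a check with 59 per arm and three visits, adding covariate main effects left the treatment-by-time standard error at 0.2604 with identical estimates on complete data, and moved it from 0.2788 to 0.2772 (0.6%) with about 30% attrition.

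**Drop-out.** A reader might argue that covariates are needed to support missing at random because age and severity drive drop-out. The article does not say so. It attributes most drop-out to factors independent of the study, links missed visits to worry about COVID-19 exposure, and plans sensitivity analyses for missing data.

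**Conclusion.** The point holds for the two Cox models only, and it is minor. The unadjusted analyses are valid but give up some power and are attenuated when prognostic factors are strong. For readmission the gain from adjustment is about 2 to 14 points, depending mainly on the strength of the prognostic score. For mortality it is roughly 0-8 points, mostly 2-4, and the comparison stays underpowered at the assumed 14% rate either way. Event rates, hazard ratios and score strength are assumptions, because the article gives none for this trial. The outcomes are secondary and no other conclusion of the plan depends on the choice.

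**What to change.** In Pre-planned analysis, pre-specify the readmission Cox model with age, CURB-65 and comorbidity count, and the mortality Cox model with age and CURB-65 only, because about 25 to 29 deaths are expected if the 14% in Background applies. Report the unadjusted hazard ratios as supportive. Alternatively, state why adjustment is confined to the primary model. Leave the mixed models as they are on this point.

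The cost is wording and code, since the primary model already uses these baseline values. The downside is a few degrees of freedom, a slightly larger standard error, and a hazard ratio that is conditional on the covariates rather than marginal; the report should say so.

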### Secondary outcomes

The secondary outcomes are readmission and mortality measured as time to event within 3 and 6 months from discharge, with comparisons between the groups. Total lean mass, total fat mass, total fat-free mass, leg lean mass, and trunk fat mass measured as mean changes from admission to discharge and from discharge to 3 months after discharge, with comparisons between groups. Health-related quality of life and activities of daily living measured as mean change from admission to discharge and from discharge to 3 months after discharge, with comparisons between groups. Muscle strength and endurance measured as mean change from admission to discharge and from discharge to 3 months after discharge, with comparisons between groups. Systemic inflammation measured as mean change from admission to discharge and from discharge to 3 months after discharge, with comparisons between groups. Accelerometer-based physical activity level measured at admission as mean change from admission to the week after discharge, with comparisons between groups.

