### Study questionnaires

At the day of inclusion (day 0), information about prior medical history, socio-demography, comorbidities (Carlson Comorbidity Index (CCI) modified by Quan [27]), smoking, and drinking habits will be collected during an initial interview and supplemented with information from the patient records. Questionnaires concerning health-related quality of life (EQ-5D-5L) [28], ability to perform daily activities (Barthel Index-100) [29], physical activity level (International Physical Activity Questionnaire [IPAQ]) [30], and frailty (FRAIL scale) will be answered in cooperation with the patient at day 1. At discharge from hospital, the questionnaires EQ-5D-5L and Barthel Index-100 will be repeated. At follow-up visits 1 and 3 months after discharge and through phone interview at 6 months after discharge the questionnaires EQ-5D-5L, Barthel Index-100, IPAQ, and Frail scale will be repeated.

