### Anthropometry and body composition

Weight is measured to the nearest 0.1 kg on an electronic scale (Seca, Hamburg, Germany). Height is measured to the nearest 0.5 cm using a stadiometer. Body mass index (BMI) is calculated as weight (kg)/height (m)^2^. Waist, hip, and arm circumferences are measured to the nearest 0.5 cm. All measurements are performed within the first 48 h of admission (day 0 or 1), at day 5, on discharge, and at follow-up visits at 1 and 3 months. Bioelectrical impedance analysis (BIA) (BioScan touch i8, Maltron International Ltd, UK) is performed at day 0 or 1, at day 5, on discharge, and follow-up visits at 1 and 3 months to assess changes in the total fat-free mass, fat mass, and body fluids/hydration. Dual-energy x-ray absorptiometry (DXA) scans (Prodigy, GE Healthcare, Nederland) are used to assess the regional distribution of lean body mass and fat mass at days 0 or 1, day 5, and follow-up visits at 1 and 3 months.

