### Muscle strength and functional ability

Muscle strength is measured using the handgrip test (SAEHAN DHD-1 Digital Hand Dynamometer, SAEHAN Corporation, South Korea) as an indicator of overall muscle strength, while the 30-s chair stand test (CST) is used to evaluate the functional ability by measuring lower body strength. Both tests are performed at days 0 or 1, day 5, on discharge, and follow-up visits at 1 and 3 months after discharge.

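### Mixed models with only patient random intercepts can misstate the confidence intervals and p values of the secondary change contrasts, in either direction, for outcomes with three or more visits

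*Protocol article*

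**What the plan says.** The Pre-planned analysis section gives one model for 11 secondary measures (five body-composition measures, EQ-5D-5L, Barthel Index-100, grip strength, chair stand, systemic inflammation and accelerometer activity): "linear mixed models with treatment by time interaction as a fixed-effects term and patient-specific random intercepts will be fitted". The next paragraph carries it over: "Likewise, for exploratory outcomes (glucose metabolism), linear mixed models with treatment by time interaction as a fixed-effects term and patient-specific random intercepts". Neither paragraph mentions a residual correlation, a visit-specific variance or robust standard errors. Log transformation is allowed for right-skewed outcomes. All results are judged at 0.05.

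The Secondary outcomes section sets the contrasts. Most of these outcomes are "measured as mean changes from admission to discharge and from discharge to 3 months after discharge, with comparisons between groups".

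The visit schedules differ by outcome:
- Grip strength and chair stand: "Both tests are performed at days 0 or 1, day 5, on discharge, and follow-up visits at 1 and 3 months after discharge".
- Bioelectrical impedance: "is performed at day 0 or 1, at day 5, on discharge, and follow-up visits at 1 and 3 months".
- DXA: "at days 0 or 1, day 5, and follow-up visits at 1 and 3 months", with no discharge scan in that list.
- EQ-5D-5L and Barthel: day 1, then "At discharge from hospital, the questionnaires EQ-5D-5L and Barthel Index-100 will be repeated", then 1, 3 and 6 months.
- Biobank inflammation samples: day 0, days 1–5, and 1 and 3 months.

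**The concern.** A random intercept with independent residuals is compound symmetry. It estimates one residual variance from all visits and applies it to every change, whichever two visits are compared. That assumption is doubtful here. Two measurements a few days apart in the same acutely ill patient will usually correlate more closely than one in hospital and one three months later. For inflammation markers, the spread during infection may also differ from the spread after recovery. A log scale may even out the variances, but it does not stop correlation from falling with time.

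This is the only analysis stated for these outcomes, and each contrast is to be reported with a confidence interval and p value. If correlation falls with time, power is lost on admission to discharge, the period when the supervised training is given. False positives then collect in the changes to 3 months. The available-case approach also relies on missing at random, and a likelihood-based mixed model has that protection only if its covariance is adequate.

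**Working it through.** **The plan's own figure.** No figure is stated for the mixed models. The sample size rests on length of stay: 2 × 3.5² × (2.241 + 0.842)² / 2² = 58.2, so 59 per arm; 59 / 0.85 = 69.4, so 70 per arm and 210 in total. It reproduces and does not depend on the mixed models.

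**Formulas.** Let V be the true covariance over J visits. With complete data:
- Model variance of any change, per patient: 2s², where s² = [trace(V) − sum(V)/J]/(J − 1), the mean variance minus the mean covariance.
- True variance of the change from visit a to visit b: V_aa + V_bb − 2V_ab.
- SE ratio r = √(model/true); actual type I error of a nominal 5% test = 2[1 − Φ(1.96r)].

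Every V below is an assumption, because the documents give none.

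**Step 1: block correlation.** Four visits (admission, discharge, 1 and 3 months), unit variances, correlation 0.8 within hospital and within follow-up, 0.5 between. Mean correlation = (2 × 0.8 + 4 × 0.5)/6 = 0.6, so 2s² = 0.8.
- Admission to discharge: true variance 2(1 − 0.8) = 0.4; r = √(0.8/0.4) = 1.414; type I error 0.6%. A contrast with 80% true power keeps Φ(2.802 − 1.96 × 1.414) = Φ(0.03) = 51%.
- Either in-hospital visit to 3 months: true variance 2(1 − 0.5) = 1.0; r = √(0.8/1.0) = 0.894; type I error 8.0%.

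**Step 2: smooth decay on the trial's own schedules.** Unit variances, correlation 0.5 + 0.4·exp(−days/30), discharge taken as day 7. Here 2s² = 2(1 − mean correlation).

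| Outcome (assumed days) | Mean corr. | Model var. | In-hospital change: true var., r, type I | Last in-hospital visit to 3 months: true var., r, type I |
|---|---|---|---|---|
| BIA, grip, chair stand (0.5, 5, 7, 37, 97) | 0.655 | 0.689 | 0.356, 1.39, 0.6% | 0.960, 0.85, 9.7% |
| DXA (0.5, 5, 37, 97) | 0.615 | 0.770 | 0.311, 1.57, 0.2% | 0.963, 0.89, 8.0% |
| EQ-5D-5L, Barthel (1, 7, 37, 97, 187) | 0.571 | 0.858 | 0.345, 1.58, 0.2% | 0.960, 0.95, 6.4% |
| Inflammation (0–5 daily, 37, 97) | 0.731 | 0.538 | 0.323, 1.29, 1.1% | 0.963, 0.75, 14.3% |

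For DXA and inflammation the in-hospital change ends at day 5, the last in-hospital time listed.

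**Step 3: other covariances, five-visit schedule.** Type I error for admission to discharge, then discharge to 3 months:
- Mild decay, 0.95 to 0.85: 1.3% and 8.6%.
- Decay from 0.8 to 0.3: 1.1% and 9.0%.
- Equal correlation 0.5, SD falling from 1.5 to 0.7: 9.7% and 1.4%, so the direction reverses.
- First-order autoregression by visit order, 0.8: 5.5% and 5.5%, with 13.4% for admission to 3 months.
- True compound symmetry: 5.0% throughout.
- Two visits only, complete data: 5.0%, whatever the variances and correlation.

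**Step 4: fitted models.** REML random-intercept fits to the first row of the table (70 per arm, 15% lost before 1 month, 400 runs) gave 1.8% for admission to discharge (7 runs, so imprecise), 10.5% for discharge to 3 months and 10.0% for admission to 3 months.

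**The case against.** The strongest reply is that the protocol names a random effect and does not exclude a residual structure or robust standard errors, and that such detail often sits in an analysis plan that is not shown. This stands in part: compound symmetry follows only if residuals are independent. But that is the ordinary meaning of the model as written, and it is stated twice as the chosen method. It is not a gap left open, and a plan that follows the sentence inherits the problem.

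A reader might infer that every mixed model here gives wrong intervals. The documents do not support that. The true covariance is unknown. Equal variances of all pairwise differences (sphericity, which is weaker than compound symmetry) are enough to remove the error. With two visits and complete data there is none. Glucose metabolism may be such a case, since the text shown does not fix the number of glucose tolerance tests.

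A reader might also infer that in-hospital effects will be missed. That holds under falling correlation but not under falling variance, where the admission-to-discharge test is too liberal.

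Two further points stand. No single schedule fits all outcomes, which is why the table works through them separately. And a plain unstructured matrix is not trivial everywhere: eight inflammation samples would need 8 × 9/2 = 36 parameters. With the mean stays of 3.9 and 6.0 days cited in the sample size section, many patients may leave before day 5, or have day 5 coincide with discharge.

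**Conclusion.** The concern holds in conditional form. For outcomes with three or more visits, the random-intercept-only model, fitted with independent residuals, puts one pooled standard error on changes over days and on changes over months, so intervals and p values can be too wide or too narrow. Under assumed decaying correlation, type I error is about 0.6% for admission to discharge and 8–10% for changes to 3 months in the block and five-visit cases. Across the schedules in the table it runs from 0.2% to 1.1% and from 6.4% to 14.3%. Even mild decay gives 1.3% and 8.6%. Size and direction rest wholly on assumed covariances. Only secondary and exploratory outcomes are touched; the primary analysis of length of stay and the sample size are not. It should be changed, because the remedy is cheap and loses little if compound symmetry happens to hold.

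**What to change.** In both mixed-model paragraphs, replace the random-intercept-only structure with an unstructured covariance across each outcome's own scheduled visits, fitted by REML with Kenward-Roger or Satterthwaite degrees of freedom.

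Where visits are many or sparse (daily inflammation samples, or a day 5 that coincides with discharge), restrict the model to the visits that define the change contrasts. Three visits need 6 covariance parameters. Restriction alone is not enough: three visits (days 0.5, 7 and 97) with a random intercept and the decay assumed above still give 0.4% and 8.1%. For DXA and inflammation, state which in-hospital measurement stands for discharge.

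As the pre-stated fallback for non-convergence, keep the random intercept with cluster-robust (sandwich) standard errors by patient.

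The cost is a few sentences. Four visits need 10 covariance parameters and five need 15, which about 180 (210 × 0.85) to 210 patients can support. The downside is possible non-convergence, which the fallback handles. The fallback repairs the standard errors but leaves the estimates resting on the simpler covariance where follow-up visits are missing, so it should not be the first choice.
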